### Additional consent provisions for collection and use of participant data and biological specimens {26b}

Not applicable as no ancillary studies are planned.

## Interventions

### Explanation for the choice of comparators {6b}

ME will be compared to placebo. Currently there are no other neuroprotectant molecules registered for use in NICU patients.

### Intervention description {11a}

The intervention will consist of double-blind administration of ME or placebo, according to a randomization list. Preterm infants eligible for inclusion after application of all the inclusion and exclusion criteria will be randomly assigned to receive 3 mg/kg/day of ME in drops or the equivalent amount of placebo in drops for 15 days. The study coordinator, after checking the list, will give the neonatologist the appropriate bottle of drops. Each bottle will be labeled “A” or “B” — in accordance with the double-blind administration protocol, neither staff nor patients (parents) will know which contain ME and which placebo, and will also show the patient’s identity, the date of the first administration, and the batch number. The neonatologist will establish and record the dose administered each evening on the basis of the patient’s weight, measured daily. A nurse will administer the drops at 11 p.m. each evening, after enteral feeding, for 15 consecutive days. This timing is intended to mimic maternal milk ME concentrations, which are highest during the night.

### Criteria for discontinuing or modifying allocated interventions {11b}

The study can be discontinued in a given trial participant due to the following: onset of AEs possibly related to the intervention, clinician judgment, or withdrawal of consent by parents.

### Strategies to improve adherence to interventions {11c}

ME/placebo will be administered for 15 days, during hospitalization in the NICUs, under the study investigators’ direct supervision and responsibility.

### Relevant concomitant care permitted or prohibited during the trial {11d}

All trial participants will receive the necessary standard of care: all treatments needed by patients, according to their clinical conditions, will be allowed. Every concomitant medication or intervention will be recorded by clinicians.

### Provisions for post-trial care {30}

A clinical and instrumental follow-up is planned until 24 months of CA, as reported in the “Intervention description” section and is part of the study. No ancillary or specific post-trial care is planned.

### Outcomes {12}

Outcomes relevant to the primary aim:
A statistically significant decrease in plasma MDA concentration (nmol/ml) in the ME-treated group after 15 days of ME/placebo administration, constituting a difference between the two groups.At the same timepoint, a statistically significant increase in plasma ME concentration (μg/mL), assumed to be responsible for the above MDA decrease, constituting a difference between the two groups.Outcomes relevant to the secondary aim: incidence, by 40 weeks of CA, of:
Cases of cerebral injury, revealed by cUS and brain MRI.Cases of ROP, auditory deficit, sepsis, BPDCases with abnormal neurological examination [25], abnormal general movements (GMs) [26], abnormal visual behavior, as assessed using the Neonatal Assessment Visual European Grid (NAVEG) [27].Outcomes relevant to the third aim:
➣ At 4–6 months of CA:
Visual function score, on the modified Fagan test [22].➣ At 18–24 months of CA:
Anthropometric measurementsNeurodevelopment and behavior, as assessed using the Griffiths Scales of Child Development 3rd Edition [28] and the Child Behavior Checklist (CBCL) [29].

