## Methods: participants, interventions, and outcomes

### Study setting {9}

The role of coordinating center will be shared by the Fondazione IRCCS Policlinico San Matteo, Pavia, and the IRCCS Mondino Foundation, Pavia, while the collaborating center will be the ASST “Spedali Civili” Children’s Hospital in Brescia (where the local ethics committee approval process is still ongoing). Preterm newborns will be recruited within 96 h of birth at the two centers’ neonatal intensive care units (NICUs). ME and placebo will be administered at these NICUs. Plasma concentrations of MDA and ME will be determined at the laboratory of the coordinating center. Staff at the collaborating center’s NICU will therefore send cryopreserved neonatal plasma samples to the coordinating center. The assessments scheduled to take place at TEA will be performed at the NICU of birth. Follow-up assessments, scheduled to take place at 4–6 months and at 18–24 months of CA, will be performed at the Child Neuropsychiatry Units of Pavia and Brescia.

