### Sample size {14}

The literature contains only one paper sufficiently similar to our study [30]; this paper was taken as a reference source to select the primary outcome (MDA concentration in the two groups) and calculate the sample size for our proposed study. A total of 26 patients per group is deemed sufficient to detect, with a power greater than 80%, a statistically significant difference equal to 8 nmol/ml (standard deviation in the two groups equal to 7) between the null hypothesis (H_0_) of the same concentration of MDA 16 nmol/ml in the two groups and the alternative hypothesis (H_1_) of an MDA concentration reduction to 8 nmol/ml in group 2 (*t*-test for independent groups with alpha error = 5%). Considering a potential dropout rate of 15%, 30 newborns per group will be enrolled.

All the participating patients will be enrolled by the two participating NICUs.

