Obstetric and perinatal data will be recorded for each infant according to the Vermont Oxford Network criteria [32]. Moreover, at TEA (40 weeks), clinical and instrumental outcomes will be evaluated by collecting/performing the following:
Anthropometric measurements;Incidence and grade of ROP, measured by indirect ophthalmoscopy (Ophthalmic Imaging System, RetCam 3, Clarity Medical Systems, Pleasanton, CA, USA);Incidence of hearing abnormality, evaluated with brainstem auditory evoked responses (Otodynamics Audiology Systems, Hatfield, Herts, UK);Incidence and severity of infection/sepsis;Incidence and severity of BPD;Results of neurological examination, conducted according to the Amiel-Tison method [25];Assessment of GMs [26];Assessment of visual behavior, performed using a new standardized tool (NAVEG) and investigating different aspects of neonatal visual function [27];Administration of the Neonatal Intensive Care Unit Network Neurobehavioral Scale [33];cUS findings: PVH/IVH as classified by Papile [23], PVL as classified by de Vries [24], and ventricular dilatation according to Ment [34] (Ultrasound model: Hitachi ALOKA Arietta V70, Hitachi Medical Systems Europe Holding AG, Zug, Switzerland, www.hitachi-medical-systems.com). cUS findings will also be classified and grouped according to Rademaker [35];Brain MRI during spontaneous sleep, performed using a 1.5-Tesla MRI scanner (Siemens) by radiographers blinded to participant allocation to the placebo or ME group; qualitative and quantitative volumetric techniques will be used to estimate overall and regional brain volumes for different tissue types; diffusion tensor imaging will be used to evaluate the integrity and maturation of WM by apparent diffusion coefficient and fractional anisotropy. Harmonization of scans at the different centers will be guaranteed.Parental stress assessment with validated surveys, as a control factor, in order to take into account the influence of parental stress on the children’s development [33]. This will be done by administering the Parental Stressor Scale: Neonatal Intensive Care Unit, the Modified Perinatal Post-traumatic Stress Disorder Questionnaire, the State Anxiety Inventory, and the Edinburgh Postnatal Depression Scale. All the surveys are validated and will be administered by trained personnel.

#### Experimental design aim 3

At 4–6 months of CA, we will collect/perform the following:

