## Statistical methods

### Statistical methods for primary and secondary outcomes {20a}

With regard to analysis of the trial results, a normality test (Shapiro-Wilk test) will be used to determine whether datasets are well modeled by a normal distribution. Categorical variables will be described as counts and percentages and compared between treatment groups by chi-squared test or Fisher’s exact test. Continuous variables will be expressed as mean and standard deviation or median and interquartile range, and comparisons between treatment groups will be made using the *t*-test for independent groups or an analogous non-parametric test if the variable is not normally distributed. Potential multivariate analysis will be performed with regression models. To account for non-independence of observations in case twins are enrolled, general estimating equations (GEE) or mixed regression models will be used. Statistical analysis will be performed by the Clinical Epidemiology and Biometry Unit at the coordinating center using the STATA statistical package (Stata, release 16 or later, StataCorp, College Station, TX, USA).

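### The cerebral-injury outcome has no new-or-worsened rule, so lesions already on the entry ultrasound can count as cases and dilute a treatment effect

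*Protocol article*

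**What the plan says.** All references are to the protocol article.

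- **Entry.** Study setting {9}: "Preterm newborns will be recruited within 96 h of birth". Under Eligibility criteria {10}, the ultrasound within that window excludes only haemorrhage above grade III and leukomalacia of grade II or more. Haemorrhage of grade I to III and leukomalacia of grade I are therefore compatible with enrolment. Sepsis is not an exclusion.
- **Outcome.** Outcomes {12} introduces the secondary set as "Outcomes relevant to the secondary aim: incidence, by 40 weeks of CA, of" a list whose first item is "Cases of cerebral injury, revealed by cUS and brain MRI". Sepsis is in the same list. The window has an end but no start.
- **Measurement at term.** Plans for assessment and collection of outcomes {18a}, aim 2, grades term ultrasound haemorrhage and leukomalacia on the two scales used for the exclusion (references 23 and 24). For infection it lists "Incidence and severity of infection/sepsis".
- **Analysis.** Under Statistical methods {20a}, categorical variables are "compared between treatment groups by chi-squared test or Fisher’s exact test". Regression is mentioned only as a possibility, with no covariate named.
- **Contrast with aim 1.** For malondialdehyde and melatonin, {18a} plans a comparison with baseline as well as between arms. Brain injury also has an entry measurement but no such provision.

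**The concern.** Aim 2 in Objectives {7} asks whether infants do better at term-equivalent age after 15 days of melatonin. A lesion present before the first dose carries no information on whether treatment prevents lesions. If it is still visible at term, the outcome as worded makes that infant a case in either arm.

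Such infants add roughly equal numbers of cases to both arms. The proportional reduction therefore looks smaller than it is among infants who could still benefit, and the comparison becomes noisier. What is at stake is a real effect on brain injury being reported as weaker than it is, or missed, when an examination already done for eligibility could separate old lesions from new ones.

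**Working it through.** **No figure in the plan to reproduce.** Sample size {14} covers the primary outcome, malondialdehyde, only. The article gives no event rate, effect size or power for cerebral injury. The one design input used here is the arm size: "Considering a potential dropout rate of 15%, 30 newborns per group will be enrolled".

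**Assumptions (not from the documents).**
- q = share of each arm with an entry lesion still visible at term and neither worsened nor resolved: 10%, 20%, 30%.
- New-lesion risk in the remaining infants: 20% on placebo, 10% on melatonin, a true risk ratio of 0.50.
- 30 infants per arm, two-sided 5%, normal approximation.

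**Counting every lesion (outcome as worded).** Arm risk = q + (1 − q) × new-lesion risk.

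- q = 10%: placebo 0.10 + 0.90 × 0.20 = 0.28; melatonin 0.10 + 0.90 × 0.10 = 0.19; ratio 0.19/0.28 = 0.68.
- q = 20%: placebo 0.20 + 0.80 × 0.20 = 0.36; melatonin 0.20 + 0.80 × 0.10 = 0.28; ratio 0.28/0.36 = 0.78.
- q = 30%: placebo 0.30 + 0.70 × 0.20 = 0.44; melatonin 0.30 + 0.70 × 0.10 = 0.37; ratio 0.37/0.44 = 0.84.

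**Counting only new or worsened lesions, all 30 infants kept.** Arm risk = (1 − q) × new-lesion risk. The ratio is (1 − q) × 0.10 / [(1 − q) × 0.20] = 0.50 for every q.

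**Power.** With n = 30, d the risk difference and p̄ the mean of the two risks, power = Φ{(d − 1.96·√[2p̄(1 − p̄)/n]) / √[(p₁(1 − p₁) + p₂(1 − p₂))/n]}.

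For q = 20%, d = 0.08 under both counts:
- Every lesion, 0.36 v 0.28: (0.08 − 1.96 × 0.1204)/0.1200 = −1.30, power 10%.
- New or worsened, 0.16 v 0.08: (0.08 − 1.96 × 0.0839)/0.0833 = −1.01, power 16%.

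| q | Ratio, every lesion | Ratio, new or worsened | Risk difference, both counts | Power, every lesion | Power, new or worsened |
|---|---|---|---|---|---|
| 0% | 0.50 | 0.50 | 10 points | 19% | 19% |
| 10% | 0.68 | 0.50 | 9 points | 13% | 17% |
| 20% | 0.78 | 0.50 | 8 points | 10% | 16% |
| 30% | 0.84 | 0.50 | 7 points | 8% | 14% |

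With all infants kept, the expected absolute difference is the same under both counts. The gain lies in the ratio and in precision, because entry lesions no longer add variance.

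**Sensitivity.** With new-lesion risks of 30% v 15%, the ratio counting every lesion is 0.64, 0.73 and 0.79 at q = 10%, 20% and 30%. Power is 20%, 16% and 12–13%, against 25%, 22% and 20% for new or worsened lesions. The direction is unchanged.

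**The case against.** **Incidence ordinarily means new cases.** This is the best reply, and it leaves the sepsis part open. A reader might infer that sepsis before the first dose is counted, but the text does not say so. Adverse event reporting {22} lists sepsis among expected events to be analysed both as results and as adverse events, which fits events arising on study. The sepsis window is unclear rather than wrong. For cerebral injury the reply is weaker: a case is whatever imaging reveals, the term scan uses the entry scales, and nothing directs the assessor to subtract what was already there.

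**The full protocol or analysis plan may define new lesions or adjust for entry grade.** It may. But Outcomes {12} is where the outcome is fixed, and its wording admits entry lesions. The point is that this wording should change, not that a detail has been left out.

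**Randomisation balances entry lesions.** In expectation, yes. A reader might infer bias, or that a chance imbalance would pass for a drug effect. With q = 20% the standard error of the between-arm difference in entry lesions is √(2 × 0.2 × 0.8/30) ≈ 10 points, which is not small. But the type I error of the planned tests already allows for such imbalance. What remains is dilution and lost precision.

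**The rates are assumed, and entry lesions may resolve or evolve.** Both stand. Resolved lesions lower q. Growth of an entry lesion after dosing could reflect treatment, which is why worsening should count. The calculation also does not apply to the continuous MRI measures (volumes, diffusion).

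**Power is low either way.** True: 19% in the illustration even with no entry lesions. That limits the practical gain.

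**The 40-week wording.** A reader might take 40 weeks of corrected age literally, as about nine months and so later than the 4–6 month visit. Objectives {7}, {18a} and the retention section {18b} show that term-equivalent age is meant. It is a slip in wording and adds nothing to the dilution argument.

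**Conclusion.** The point holds for cerebral injury on ultrasound. As worded, the outcome lets lesions present at entry count as cases, and the planned unadjusted test does nothing to remove them. The consequence is attenuation towards no effect and some loss of precision, not systematic bias.

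The size cannot be taken from the documents. The range of 0.68 to 0.84 instead of 0.50 is an illustration. It rests on assumed entry-lesion shares of 10% to 30%, on those lesions persisting unchanged to term, and on halving a 20% new-lesion risk. The documents do not support saying that pre-dose sepsis is counted, that the comparison is biased, or that the timing of the term assessment is in doubt.

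The outcome is secondary and the trial is not sized for it, so the main conclusion on malondialdehyde is unaffected. The change is still worth making before unblinding.

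**What to change.** 1. In Outcomes {12}, define an ultrasound case of cerebral injury as a lesion that is new, or worse in grade, compared with the entry ultrasound.
2. Keep every randomised infant in the analysis, as {20c} already requires. Infants with an entry lesion stay in the denominator and become cases only if it worsens. No change to eligibility is suggested.
3. Name entry ultrasound grade as a covariate in the models for the MRI and developmental outcomes.
4. Tabulate entry lesions by arm with the baseline data.
5. As clarifications, state that sepsis counts from the first dose, and replace 40 weeks of corrected age with term-equivalent age, as in Objectives {7} and {18a}.

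**Cost.** Mostly wording. The entry ultrasound is already done for eligibility. The article does not say that sepsis onset dates are recorded, so the case report form must be checked for item 5. The small statistical downside is fewer events: at q = 20% in the illustration, the expected placebo cases among 30 infants fall from 30 × 0.36 = 10.8 to 30 × 0.16 = 4.8. Power is nevertheless higher, because the cases removed carried no treatment effect.

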### Participant timeline {13}

See Table 1.

### Sample size {14}

The literature contains only one paper sufficiently similar to our study [30]; this paper was taken as a reference source to select the primary outcome (MDA concentration in the two groups) and calculate the sample size for our proposed study. A total of 26 patients per group is deemed sufficient to detect, with a power greater than 80%, a statistically significant difference equal to 8 nmol/ml (standard deviation in the two groups equal to 7) between the null hypothesis (H_0_) of the same concentration of MDA 16 nmol/ml in the two groups and the alternative hypothesis (H_1_) of an MDA concentration reduction to 8 nmol/ml in group 2 (*t*-test for independent groups with alpha error = 5%). Considering a potential dropout rate of 15%, 30 newborns per group will be enrolled.

All the participating patients will be enrolled by the two participating NICUs.

### Recruitment {15}

The recruitment will be done at Fondazione IRCCS Policlinico S. Matteo, Pavia, Italy (joint coordinating center) and ASST "Spedali Civili” di Brescia, Brescia, Italy (participating center). The coordinating center obtained the necessary legal permission to start the trial earlier than the participating center, which is currently awaiting ethical approval. Both hospitals are third-level centers and accept newborns from 23 weeks of GA onwards. The principal investigator (PI) and the other neonatologists participating in the trial actively work on the wards, with schedule timing that guarantees the constant presence (24 h per day) of the PI or at least one of the co-investigators responsible for recruiting patients, giving adequate information to parents, and following the ongoing study. The centers have an incidence of about 4 to 8 eligible patients/month (patients with GA ≤ 29 weeks + 6 days, able to receive 20 ml/kg/day enteral feeding within 96 h of birth). This should guarantee recruitment of a total of 60 patients (even accounting for dropouts).

The two centers are similar in terms of available instruments, and both have a dedicated child neurology and psychiatry service. The researchers involved in the study have similar high levels of expertise, underwent the same specialist training, and use same methodological tools. Furthermore, most of them have often worked together on other research projects over the past years.

## Assignment of interventions: allocation

### Sequence generation {16a}

The randomization will be generated by the Unit of Clinical Epidemiology and Biometry (unblinded team) at the coordinating center, according to a 1:1 allocation ratio, by means of computer-generated random numbers that will allow for extra patient allocations in the event of dropouts. The randomization sequence will be generated by a random number generator at the same unit. The PIs of the two NICUs will sequentially allocate the participants to the two groups on the basis of the generated lists.

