### Concealment mechanism {16b}

The Clinical Epidemiology and Biometry Unit staff generating the randomization list will serve as the unblinded team, responsible for generating and also storing the randomization list and for communicating with other co-investigators or with ME/placebo suppliers if necessary. ME/placebo will be kept in anonymous vials, bearing alpha-numeric codes, lot numbers, and expiration dates. These vials will be logged and stored in a locked room at each NICU.

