### Implementation {16c}

The local study coordinator, after checking patient’s eligibility and randomization list, gives the appropriate bottle of drops to the neonatologist. Each bottle will be labeled “A” or “B” and will also indicate the patient’s identity, the date of the first administration, and the batch number.

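### Allocation concealment is not assured as written: recruiting investigators allocate from the randomization lists, and the sections disagree on who has access to the list and how the drug is labelled

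*Protocol article*

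**What the plan says.** Five sections of the protocol article bear on this point.

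- **Sequence generation {16a}.** The source of the sequence is clear: "The randomization will be generated by the Unit of Clinical Epidemiology and Biometry (unblinded team) at the coordinating center, according to a 1:1 allocation ratio". The section then says who uses it: "The PIs of the two NICUs will sequentially allocate the participants to the two groups on the basis of the generated lists".
- **Implementation {16c}.** At the site, "The local study coordinator, after checking patient’s eligibility and randomization list, gives the appropriate bottle of drops to the neonatologist". The bottle carries one of two letters, A or B, with the infant's identity, the first dosing date and the batch number.
- **Intervention description {11a}.** The same step appears again: "The study coordinator, after checking the list, will give the neonatologist the appropriate bottle of drops". This section adds that staff and parents will not know which letter is melatonin.
- **Concealment mechanism {16b}.** The Biometry Unit is "responsible for generating and also storing the randomization list". Vials are described as anonymous, with alpha-numeric codes, and are kept in a locked room at each NICU.
- **Recruitment {15}.** Round-the-clock presence is promised of "the PI or at least one of the co-investigators responsible for recruiting patients, giving adequate information to parents, and following the ongoing study". The consent section likewise has participating NICU clinicians recruit and take consent.

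**The concern.** Concealment and blinding are separate safeguards. Concealment protects the moment of entry: whoever decides whether and when an infant joins should not be able to foresee the group that the infant will join. Blinding protects what happens afterwards.

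The article's wording puts recruiting and allocating in the same hands, those of the PIs. It also gives the person who checks eligibility a reason to look at the list. Entry to this trial leaves room for judgement: whether an infant can take the required enteral volume, when parents are approached, and where in the 96 h window the infant is enrolled. If the next group code can be foreseen, those decisions can depend on it, deliberately or not. The two groups of 30 might then differ at baseline for reasons other than chance, and the comparison of malondialdehyde and of all later outcomes would inherit that difference.

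**Working it through.** The point depends on no figure in the plan, so the check sets the sections side by side.

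**1. Who has access to the list?** Concealment mechanism says the Biometry Unit stores it. Sequence generation has the PIs allocate from the lists. Implementation and Intervention description have a coordinator check the list. The first statement fits the other three only if PIs and coordinators get each entry from the Unit one at a time. The article does not say so.

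**2. Do the same people recruit and allocate?** For the PIs, yes: Recruitment and Sequence generation give them both tasks. The coordinator is documented as checking eligibility, consulting the list and handing over the bottle, but not as recruiting. Only the coordinator hands over bottles.

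**3. Does the order of steps protect the next entry?** Implementation names eligibility before the list. Intervention description places assignment after all criteria have been applied, and signed consent of both parents is one of those criteria. So the current infant's entry appears to be looked up after that infant qualifies. This order does not protect the following infant. If what is consulted is a list rather than a single released entry, looking up one line can expose the next. Nothing in the article rules this out.

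**4. What would a visible entry reveal?** Bottles carry only A or B, so the next letter is the next group. Concealment mechanism describes alpha-numeric vial codes instead. If those codes were unique to each vial, a visible code would reveal much less. The two labelling descriptions cannot both be the operative one without further explanation.

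**5. How robust is ignorance of what A means?** The article allows urgent unblinding for safety, carried out by the Unit and shared only with those who need to know. With two letters fixed for the whole trial, learning one infant's treatment gives the meaning of both letters, and so the treatment of every infant on the list, past and future. A correct guess from one infant's course would do the same.

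**6. Scope.** The procedure applies to every allocation: 2 arms × 30 = 60 infants at two NICUs.

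**The case against.** The strongest reply has four parts.

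- **Custody.** The Unit is named as keeper of the list and as communicating with co-investigators, so checking the list could mean asking the Unit. A reader might infer that the sites hold the list; no section says so, and that reading should not be adopted. What remains is an unresolved conflict over access.
- **Foreknowledge.** A reader might also infer that the next assignment is known with certainty before enrolment. The documents do not support that either. No section has anyone view the list before consent, and staff are stated not to know which letter is melatonin. Someone who sees A without knowing its meaning cannot knowingly favour melatonin. This stands, but it is a blinding argument. Steering by letter can still make the groups differ, and the ignorance is fragile with two fixed letters.
- **Size.** It is tempting to put a number on the bias by supposing that recruiters sort infants by malondialdehyde. That value comes from a laboratory assay of a sample taken at recruitment, and nothing shows that recruiters have it when deciding entry. Any such figure would be invented. Baseline malondialdehyde is collected and regression models are foreseen, so adjustment could remove part of an imbalance, though not selection on unmeasured prognosis.
- **Condensed article.** The full protocol may describe a release step. An omitted detail would be no finding. The point here rests on what the article affirmatively states: recruiting PIs allocate from lists, and other sections say something incompatible about storage and labels.

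**Conclusion.** The point holds in this form: allocation concealment is not assured as written, and Intervention description, Sequence generation, Concealment mechanism and Implementation conflict on list access and labelling. Following the text literally could let recruiting investigators foresee the next group code, and no described step prevents it.

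The conclusion does not require that the sites hold the list, that anyone has looked ahead, or that staff know which letter is melatonin. It rests on two readings: that the PIs who allocate are the PIs who recruit, as the sections state, and that A and B keep the same meaning throughout the trial, as the two-letter scheme implies. If the letters differed between centres, one decoding would reveal one centre's list rather than both.

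No magnitude in nmol/ml can be derived. The exposure is the entry decision for all 60 infants. Later adjustment would be only a partial remedy, so the protection has to be in place at allocation.

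**What to change.** - State that the Biometry Unit alone holds the list. It releases one unique kit number for one infant, and only after eligibility and both parents' consent have been recorded.
- If the Unit cannot cover 24 h, have it supply sequentially numbered, identical, pre-packed kits, to be used strictly in order.
- Replace the A and B labels with unique kit codes, so that unblinding one infant reveals nothing about any other.
- Remove list access from PIs and coordinators: delete the statement in Sequence generation that PIs allocate from the lists, and the list check in Intervention description and Implementation.
- Reconcile those three sections with Concealment mechanism, so that one account of custody, release and labelling applies throughout.

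The cost is procedural wording, some relabelling and a short delay per enrolment, which must fit the 96 h window. Sample size, endpoints and analysis do not change. The change protects only infants enrolled after it is made.
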